### Randomization

Upon individual completion of the check-in survey by both partners, couples are randomized to either the control arm (Individual Counseling) or the intervention arm (Couples Counseling). The treatment assignments are generated with the use of one pseudo-random number generator across all three study sites. The randomization process generates a random number between 0 and 100. If given an odd number, the couple is placed in the control treatment group; if given an even number, the couple is placed in the intervention treatment group.

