#### Session One

CHTC sessions are conducted by a counselor who is trained in CHTC and last approximately 30-45 minutes. Only the HIV-negative partner is tested during the session. Posttest counseling focuses on dyadic prevention messages, and revisits the couple’s HIV risk concerns and sexual agreements in light of their test results. While focusing on the needs of the HIV-positive partner is necessary, the discussion also emphasizes how the couple can work together to keep the HIV-positive partner healthy and reduce transmission risks within the relationship. The prevention counseling element of the CHTC session focuses on talking to the couple about prevention options (including PrEP) and asking them to consider which prevention options may work best based on their relationship needs, context, and unique risk profile.

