### Statistical Analyses

The analysis employs an intent-to-treat analysis design. The percentage of HIV-positive individuals who achieve viral suppression and report being fully engaged in care will be compared across arms, using Chi-square tests for significant difference. Retention in care is measured as the number of 6-month blocks during which at least one clinic visit was attended over the 2-year period following an initial attended visit; the percentage of HIV-positive individuals who report full retention in care (one clinic visit during each 6-month block) and the number of 6-month blocks during which care was received will be compared across study arms, using the appropriate tests for statistical significance. The capability of the intervention to yield longer-lasting effects in adherence endpoints over time will be examined. The visual analog scale data over the course of the study, at baseline and follow-up, will be analyzed using generalized linear models (GLMs) with properly-chosen (based on the distribution of dependent variables) link functions to analyze longitudinal adherence outcome data. The GLMs will be estimated using generalized estimating equations (GEE) with robust standard error estimates, which provide an extension of regression analyses to the cases of correlated or repeated observations and allows for inclusion of both categorical and count-dependent variables, and for appropriate modeling of covariance structures when observations are correlated across time. With appropriate link functions, GLMs can readily handle dependent variables with normal distributions, dichotomous outcomes, count data (Poisson distribution), and over-dispersed or zero-inflated count data (negative binomial models). The models will include the dyadic characteristics scales to examine the extent to which adherence is shaped by relationship functioning.

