The analysis will also examine conceptual mediators and epidemiologically identified moderators. If the Stronger Together intervention works to increase viral suppression and number of participants reporting full engagement in care among the intervention sample in significantly greater magnitude than the comparison condition, we will assess the extent to which this relationship works through several possible mediators, including dyadic factors and relationship functioning (ie, communication). For mediation analyses, we will employ MEDIATE procedures. MEDIATE estimates the total, direct, and indirect effects of causal variable(s) on the outcome variable through a proposed mediator variable or set of mediator variables. For effect modification (moderation) analyses, we will add interaction terms one-by-one for the intervention condition and the potential moderators (eg, age, race/ethnicity, and psychosocial factors such as depression and length of relationship). Significant or large interaction terms would suggest that the effects of the intervention differ for different subgroups, as defined by the moderators.

The analysis will also examine HIV sero-conversion among HIV-negative partners and syphilis as secondary outcomes: the prevalence and 24-month cumulative incidence of HIV and syphilis will be examined in aggregate and then by study arm. During the interim assessment visits (that occur before month 12 and then again before month 24) we will collect information on STI testing/diagnosis/treatment that participants received elsewhere since their last study assessment visit. These data will be used to adjust analyses. Using Cox proportional hazard regression models, we will assess if intervention status results in decreased odds (hazard ratio) of HIV and STI infection, separately, over the 24-month period.

The safety of the intervention at the individual level will be assessed by examining reported IPV within the relationship and relationship dissolution. Prevalence of each individual adverse outcome or any adverse outcome will be calculated, and prevalence of outcomes will be compared in the control and intervention groups using Chi-square tests or Fischer’s exact tests, as appropriate.

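### Adjusting the HIV and syphilis/STI comparisons for testing, diagnosis and treatment received elsewhere after randomisation can bias the hazard ratio, and in the syphilis/STI model can condition on the outcome

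*Protocol article*

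**What the plan says.** The relevant text is the HIV and syphilis paragraph at the end of the section on incidence of at-risk sex in the protocol article. It introduces the endpoints: "The analysis will also examine HIV sero-conversion among HIV-negative partners and syphilis as secondary outcomes". It then says that at interim visits, before month 12 and again before month 24, "we will collect information on STI testing/diagnosis/treatment that participants received elsewhere since their last study assessment visit". The use of these data is given in one sentence: "These data will be used to adjust analyses". The model follows at once: "Using Cox proportional hazard regression models, we will assess if intervention status results in decreased odds (hazard ratio) of HIV and STI infection", with HIV and STI analysed separately over 24 months.

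The article does not say how the data enter the analysis. It does not limit them to finding or dating cases, and it does not name an unadjusted hazard ratio as the main result.

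Three other places bear on the point:
- **Randomization:** "Upon individual completion of the check-in survey by both partners, couples are randomized". This is before any follow-up visit.
- **Statistical Analyses:** "The analysis employs an intent-to-treat analysis design".
- **Session One:** the prevention counselling in the intervention arm "focuses on talking to the couple about prevention options (including PrEP".

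**The concern.** A covariate measured after randomisation is safe in an arm comparison only if assignment does not affect it. Here assignment might. The intervention counsels couples on prevention and on engagement with care, and the Introduction describes a causal path through health-enhancing behaviour to lower STI and HIV incidence. Outside testing and treatment may lie on that path.

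Two problems follow if these variables enter the Cox models.

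1. **Both models.** If higher-risk men test more, and the intervention also raises testing, holding testing fixed compares unlike men. Within testers, and within non-testers, the intervention arm then contains men of lower average risk. The hazard ratio drops below its true value, so an ineffective intervention can look protective. If testing or treatment is also a route by which the intervention works, adjustment removes part of the total effect.
2. **The syphilis/STI model only.** A syphilis infection diagnosed elsewhere is an STI event. Using that diagnosis as a covariate puts part of the outcome on both sides of the model.

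The hazard ratio by arm would then no longer estimate the effect of assignment.

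**Working it through.** The article states no figure on this point, so there is none to reproduce. The check has three parts.

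**1. Timing and role of the variables**

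| Question | Place in the article | Answer |
|---|---|---|
| When are couples randomised? | Randomization | After check-in at the baseline visit |
| When are the outside-care data collected? | HIV and syphilis paragraph | At interim follow-up visits |
| Could assignment change them? | Introduction; Session One | Plausibly, through prevention and care counselling |
| Can they contain the HIV event? | Biomedical Measures | No: the data concern STI care, and HIV is tested by the study at each assessment |
| Can they contain the syphilis/STI event? | HIV and syphilis paragraph | Yes, through an outside syphilis diagnosis |

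**2. Direction and possible size of the bias**

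Every input to this simulation is an assumption; none is in the article. There were 1,000,000 participants per scenario, allocated 1:1 (A = 0 or 1), with an unmeasured risk factor U distributed as standard normal.
- Outside testing T: logit P(T) = −0.8 + d·A + 0.8·U, with d = 0, 0.5 or 1.0.
- Monthly hazard: [−ln(1 − 0.10)/24] × HR^A × exp(0.6·U), followed for 24 months. This is a 10% control risk at average U.
- Outside diagnosis D, among outside testers: 60% of infections, plus 10% with another STI diagnosis.
- Fit: Poisson regression of the event with follow-up time as exposure, equivalent here to an exponential hazard model.

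| True HR | d (log odds ratio, arm on testing) | Unadjusted | Adjusted for testing | Adjusted for diagnosis | Adjusted for both |
|---|---|---|---|---|---|
| 1.0 | 0 | 1.00 | 1.00 | 1.00 | 1.00 |
| 1.0 | 0.5 | 1.00 | 0.96 | 0.93 | 0.96 |
| 1.0 | 1.0 | 1.00 | 0.92 | 0.87 | 0.93 |
| 0.7 | 0 | 0.71 | 0.71 | 0.72 | 0.73 |
| 0.7 | 0.5 | 0.71 | 0.68 | 0.68 | 0.70 |
| 0.7 | 1.0 | 0.71 | 0.65 | 0.63 | 0.67 |

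The unadjusted estimate stays at its target throughout. If the arm has no effect on outside testing, adjusting for testing does no harm. Once it has one, adjusting for testing or diagnosis alone lowers the hazard ratio below the unadjusted value. Adjusting for diagnosis shifts the estimate slightly (0.71 to 0.72) even at d = 0 when there is a true effect, because the covariate is partly the outcome.

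The table is not a bound. With a stronger shared risk factor (logit P(T) = −0.4 + 0.8·A + U; yearly hazard 0.05·exp(U); 2 years), outside testing is 58% v 42% and a true HR of 1.00 becomes 0.89 after adjustment for testing.

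**3. Scale of the endpoints**

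From Sample Size: 165 couples × 0.80 retention / 2 = 66 couples per arm, hence 66 HIV-negative partners per arm. With assumed 24-month control incidence p, expected events = 66p + 66[1 − (1 − p)^HR].
- p = 2%, HR 0.5: 1.3 + 0.7 = 2.0 events.
- p = 15%, HR 0.7: 9.9 + 7.1 = 17.0 events.

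Power by Schoenfeld's formula, Φ(½·√events·|ln HR| − 1.96), runs from about 5% to 27% for HR 0.5 to 0.7. At 17 events SE(ln HR) ≈ 2/√17 = 0.49, so the 95% limits are the estimate divided and multiplied by exp(1.96 × 0.49) ≈ 2.6. The syphilis denominator differs, because all participants are tested for it but only in Atlanta and Chicago. The 66 per arm applies to HIV.

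**The case against.** **The sentence may mean ascertainment.** This is the best argument against the point. Reports of care received since the last visit are what one would need to catch infections found between visits. Boston does no study syphilis testing (Data Collection; Biomedical Measures), so outside reports are the only stated route to a syphilis event there. Where the article means covariates, for at-risk sex, it names baseline ones. The reading is plausible and the article does not exclude it. But the sentence says adjust, it covers testing and treatment as well as diagnosis, and it stands directly before the Cox models. If ascertainment was meant, the wording misstates it and the same sentence needs changing.

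**Stronger readings that the article does not support:**
- *That the HIV model also conditions on its outcome.* It does not. The data concern STI care, an outside STI diagnosis is not a sero-conversion, and the two endpoints are modelled separately.
- *That the rule contradicts the intention-to-treat statement.* Adjustment moves nobody between arms. It changes what the hazard ratio estimates, which is a different criticism.
- *That the comparison is certainly biased, by a known amount.* No outside-testing rate is given. Without an arm effect on testing, the simulation shows no bias at the null.
- *That a Cox model with outside diagnosis as a covariate cannot be fitted.* This happens if every outside diagnosis is assumed to be an event. Once other STI diagnoses are allowed, as in the table, the model fits.

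**Consequence is limited.** These are secondary outcomes, and Sample Size concedes insufficient power. With limits a factor of about 2.6 either way, a shift from 1.00 to 0.87 would not be visible in this trial's data. That lowers the priority. It does not justify an avoidable bias in an estimate that the article plans to produce.

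**Counting outside diagnoses has its own bias.** If the intervention raises outside testing, more events, and earlier ones, would be found in that arm. This stands, and the fix must provide for it.

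**Conclusion.** The point holds as a fault in one stated rule, worth correcting but of modest consequence. As worded, the plan adjusts the HIV and syphilis/STI analyses for variables that arise after randomisation and that the intervention could change. Used as Cox covariates, they can bias the arm comparison. In the syphilis/STI model an outside diagnosis can also be the event under study.

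The size cannot be stated for this trial. For assumed log odds ratios of 0 to 1.0 for arm on outside testing, a true hazard ratio of 1.00 becomes 1.00 to about 0.92 when adjusted for testing, and 1.00 to about 0.87 when adjusted for diagnosis. The direction, towards a false benefit, rests on two assumptions: higher-risk men test more, and the intervention increases testing. The primary outcomes, engagement in care and viral suppression, are not affected.

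**What to change.** Replace the adjustment sentence with a rule along these lines:

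> The comparison of HIV and of syphilis/STI infection between arms will be unadjusted, or adjusted for baseline covariates only. STI testing, diagnosis and treatment received elsewhere will not be entered as covariates in this comparison. Syphilis diagnoses made elsewhere will be used only to ascertain and date events, by the same rule in both arms. Outside testing will be reported by arm. Because detection outside the study may differ by arm, a sensitivity analysis will count only infections detected by scheduled study testing (for syphilis, at Atlanta and Chicago). Any analysis that conditions on outside testing or treatment will be labelled as a sensitivity or mediation analysis.

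The cost is one sentence replaced by a short paragraph, plus one sensitivity analysis. The planned data should suffice, with one point to check: the article does not say that dates of outside diagnoses are recorded. If they are not, the rule must state how such events are dated, identically in both arms.

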### Data Collection

After a couple gives informed consent, but before the couple is randomized to either the intervention or control group, each member of the couple is given a baseline survey. This survey is approximately 60-90 minutes long and collects data on demographics, relationship characteristics, sexual history, HIV care, and HIV prevention. In addition to survey data, biological samples are collected: STI testing, ART/preexposure prophylaxis (PrEP) drug adherence testing, and viral load testing. At the Boston site, however, STI testing is not conducted due to budgeting constraints.

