### Biomedical Measures

For HIV-negative partners, HIV sero-status is tested at each study assessment. For HIV-positive partners, viral load and ART levels are measured at each study assessment and collected via dried blood spots. All participants are tested for syphilis at each study assessment in the Atlanta and Chicago sites. Budgetary constraints prevented testing for other STIs, as well as syphilis testing, in the Boston site.

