### Dyadic Characteristics: Analysis of the Scale Data Over Time

Repeated-measures analyses using mixed linear models will be performed for scale data. These analyses will include participant-level characteristics and couple-level variation or clustering. Participants will be nested within couples with the participant as the experimental unit. Repeated-measures analyses for each scale will be analyzed with a means model with SAS Proc Mixed providing separate estimates of the means by time on study and treatment group. An unstructured variance-covariance form among the repeated measurements will be assumed for each outcome, and estimates of the standard errors of parameters will be used to perform statistical tests and construct 95% confidence intervals. T-tests will be used to compare the pairwise differences between the model-based treatment means (least-squares means) at each time point. Statistical tests will be 2-sided. The model-based means are unbiased with unbalanced and missing data if missing data are noninformative (missing at random). A dropout process is assumed to be missing at random if, conditional on the observed data, the dropout is independent of the unobserved measurements.

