### Incidence of Aggregate “Sex at Risk” Within Partnerships

At-risk sex will be defined as any CAI that occurs within the partnership during the follow-up period, even if the HIV-negative partner is taking PrEP or the HIV-positive partner has achieved viral suppression, in accordance with current CDC recommendations on PrEP and condom use [65]. The incidence of at-risk sex acts will be calculated as an incidence density, with the numerator being number of individual at-risk sex acts, and the denominator being person-years of follow time. Comparisons of the incidence of at-risk sex acts will be made by comparing incidence densities between the two arms. Incidence rates per couple-year of follow-up will be estimated and compared using exact methods based on the Poisson distribution when there are fewer than 15 events per subgroup or, when there are at least 15 events per group, by using the GEE approach. Baseline covariates include race, age, and duration of relationship. Period incidence rates (6-monthly incidence density rates) of at-risk sex will be estimated by performing a GEE Poisson regression analysis of the 6-monthly counts, implemented using the SAS PROC GENMOD procedure [66], and using an exchangeable correlation structure for the repeated observations of couples. The incidence density ratio (or incidence rate ratio; IRR) is the ratio of the incidence density in one treatment group (intervention arm) to that of a control group (standard of care). Results by each baseline covariate will be summarized as the IRR and the 95% confidence interval. In addition, we will tabulate data on disclosure of sex outside the relationship, the percentage of couples with agreements about sex outside the relationship, and the percentage of couples reporting agreement breakage or change in agreements. Prevalence of each outcome will be calculated, and prevalence of outcomes will be compared in the control and intervention groups using Chi-square tests or Fischer’s exact tests, as appropriate.

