### Sample Size

Estimating 80% retention, we propose to enroll a sample of 165 male sero-discordant couples. The primary outcomes are engagement in HIV care and viral suppression. A sample of 165 sero-discordant couples provides statistical power (with 95% confidence and 80% power) to detect scientifically significant relative differences of 15%, 20%, and 25% in each of these outcomes between the two study arms. Additional health-enhancing behaviors include recent sexual risk-taking; using the data from our previous RCT of CHTC, this sample of 165 sero-discordant couples provides statistical power to identify significant differences in sexual risk-taking between the two arms. Using the methods described by Rosner for sample size estimation for longitudinal studies [67], a sample size of 75 couples in each group will ensure statistical power (using a two-sided two-sample t-test) to identify differences in the dyadic scale constructs between arms. As secondary outcomes, the study will examine sero-conversion and syphilis incidence between the two arms, although the power is insufficient to detect significance differences between the study arms.

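### The syphilis/STI Cox model states no allowance for the randomised couple; fitted in its ordinary form, it would understate the standard error of the arm comparison

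*Protocol article*

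**What the plan says.** The Randomization section of the protocol article allocates whole couples to an arm, so both partners always share the same assignment.

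The infection outcomes are described near the end of the Methods, in the section on the incidence of at-risk sex within partnerships: "The analysis will also examine HIV sero-conversion among HIV-negative partners and syphilis as secondary outcomes". The model for the comparison by arm is then named: "Using Cox proportional hazard regression models, we will assess if intervention status results in decreased odds (hazard ratio) of HIV and STI infection, separately". No variance estimator, frailty term, couple-level event definition or unit of analysis is given.

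Biomedical Measures says who is tested: "All participants are tested for syphilis at each study assessment in the Atlanta and Chicago sites". Boston contributes no study tests for syphilis; Data Collection states: "At the Boston site, however, STI testing is not conducted due to budgeting constraints".

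Other analyses do say how dependence is handled. For the dyadic scales: "These analyses will include participant-level characteristics and couple-level variation or clustering", with participants nested in couples. For longitudinal adherence, Statistical Analyses specifies GEE with robust standard errors. For the six-monthly counts of at-risk sex, the Poisson GEE is fitted "using an exchangeable correlation structure for the repeated observations of couples".

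Sample Size says that power is insufficient to detect differences between the arms in sero-conversion and syphilis.

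**The concern.** In Atlanta and Chicago the syphilis analysis can hold two men per couple, always in the same arm. Syphilis is sexually transmitted, so infection in one partner raises the risk in the other, and the two event times should be positively correlated. The trial's own rationale in the Introduction links risk-taking inside the relationship to STI incidence.

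The Cox model in its usual form bases its standard error on independent subjects. An infection passed from one partner to the other would then count as two independent pieces of evidence for or against the same arm. The hazard ratio would carry too narrow an interval, and a chance imbalance of a few couples could look like a protective or harmful effect. Low power does not guard against this, because power and the false-positive rate are separate properties and the comparison by arm is still planned.

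**Working it through.** **The plan's own figure.** The article gives no event number, syphilis incidence, within-couple correlation or error rate for the Cox models, so there is nothing to reproduce.

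**Inputs from the article**
- Unit of randomisation: the couple, so cluster size m = 2 (Randomization).
- Men in the syphilis model: both partners, at two of three sites (Biomedical Measures, Data Collection).
- Nominal level: 5%, taken from "with 95% confidence and 80% power" in Sample Size, where it is stated for the primary outcomes. Two-sided tests are stated in the scale-data section. Applying both to the Cox model is an assumption.
- Target enrolment: 165 couples (Sample Size).

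**Assumptions, not in the article**
- Within-couple correlation rho: a range is shown, with 0.1 to 0.5 as the working range.
- For the simulation only: equal enrolment by site, giving 165 × 2/3 = 110 couples in Atlanta and Chicago, and a 24-month cumulative incidence of 10% or 20%.

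**Step 1: design effect.** With both members of a pair in the same arm, the variance of the arm comparison is multiplied by 1 + (m − 1) × rho = 1 + rho. The true standard error is therefore sqrt(1 + rho) times the one an ordinary fit reports. The reported interval, on the log hazard scale, has 1/sqrt(1 + rho) of its correct width.

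**Step 2: false-positive rate.** A nominal 5% test rejects when the naive statistic exceeds 1.96, so its true rate is 2 × (1 − Phi(1.96 / sqrt(1 + rho))).

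| rho | 1 + rho | Interval width relative to correct | True false-positive rate |
|---|---|---|---|
| 0 | 1.0 | 1.000 | 5.0% |
| 0.1 | 1.1 | 0.953 | 6.2% |
| 0.2 | 1.2 | 0.913 | 7.4% |
| 0.3 | 1.3 | 0.877 | 8.6% |
| 0.5 | 1.5 | 0.816 | 10.95% |
| 0.7 | 1.7 | 0.767 | 13.3% |
| 1.0 | 2.0 | 0.707 | 16.6% |

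**Step 3: check by simulation.** The set-up was 110 couples, couple-level 1:1 randomisation, no effect of arm and 3,000 runs per setting. It compared the ordinary Cox score (log-rank) test with the same test using a variance clustered on the couple. The first figure in each cell is for 10% incidence (about 22 events), the second for 20% (about 44 events).

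| rho | Ordinary | Couple-clustered |
|---|---|---|
| 0 | 4.5% / 4.9% | 4.5% / 4.9% |
| 0.1 | 6.2% / 6.2% | 4.8% / 5.2% |
| 0.2 | 7.8% / 7.1% | 4.7% / 4.6% |
| 0.3 | 7.5% / 8.1% | 3.8% / 4.5% |
| 0.5 | 11.1% / 11.6% | 4.3% / 5.5% |

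The Monte Carlo standard error near 5% is sqrt(0.05 × 0.95 / 3000) = 0.4 percentage points. The simulation agrees with the formula, and clustering brings the test back close to its nominal level.

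**Step 4: which analyses are affected.** HIV sero-conversion can occur only in the HIV-negative partner, so that Cox model has one man per couple. The primary outcomes concern only the HIV-positive partner, again one man per couple. The two-partner problem arises only in the syphilis/STI model.

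**The case against.** The strongest objection is that the article is silent on the point, and silence is not a decision. A clustered variance, a shared frailty or a first event per couple would each be compatible with the sentence as written. A condensed article may leave the variance option to the full protocol or the analysis plan, neither of which is shown. The authors plainly know about partner clustering, since they state it for the scales.

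This stands against the stronger reading that a reader might infer: that the trial will analyse the partners as independent and so will report a doubled false-positive rate. The documents do not show that. What remains is that the article gives dependence details for its other correlated analyses and here names a model whose default ignores the couple. Anyone who follows the text literally gets the wrong standard error.

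Three further objections have weight.
- A doubled error rate needs rho near 0.5, which is an assumption. At 0.1 to 0.2 the formula gives 6.2% to 7.4%.
- The exchangeable structure in the at-risk-sex analysis is a weak precedent. It covers repeated observations of a couple over time, not two partners entered separately. The scale analysis is the proper comparison.
- The 1 + rho formula supposes that both men contribute full follow-up. HIV-negative partners are censored after one more visit when a couple separates, but with 13 of 160 couples (8%) separated, the reduction is small.

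The article names no test or interval for by-arm syphilis prevalence and cumulative incidence, so clustering matters there only if one is reported.

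**Conclusion.** The point holds in conditional form. The syphilis/STI Cox model states no allowance for the couple. If it is fitted in its ordinary form with both partners entered, the true standard error is sqrt(1 + rho) times the reported one: 1.05 times at rho = 0.1 and 1.22 times at rho = 0.5. Over that assumed range the two-sided false-positive rate is about 6% to 11% instead of 5%. The direction rests on positive correlation between partners, which is well founded for an infection they can pass to each other. The size rests on a correlation that the documents do not give.

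The priority is minor. The point touches one secondary outcome at two of three sites, already declared underpowered. It gives no ground to doubt the primary outcomes or the HIV model.

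**What to change.** In the paragraph on HIV and syphilis, add that the syphilis/STI Cox model uses a robust (sandwich) variance clustered on the couple, for example PROC PHREG with COVS(AGGREGATE) and the couple as ID, and that the hazard ratio is reported with that interval. Use the same clustering for any interval or test given for by-arm syphilis prevalence or 24-month cumulative incidence. Leave the HIV model as it is. If the full plan already does this, the added sentence simply reports it.

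The cost is one sentence and one program option, with no new data. The interval becomes wider, by a factor of about 1.05 to 1.22 on the log hazard scale for rho of 0.1 to 0.5, for an outcome whose power is already low.

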#### Process and Use of Communal Coping

Several scales are used to measure this element. The *Outcome Efficacy to Reduce HIV Threat Scale* discusses how communal coping involves couples working together and making decisions to reduce the health threat. Three subscales were created to capture the full range of outcome efficacy related to these three processes of communal coping. For the first subscale, *Joint Effort*, the stem, “My partner and I believe that ‘working together’ versus on our own is an effective strategy” is used. For the second subscale, *Communication*, the stem, “Communicating with my partner is an effective strategy for” is used. For the third subscale, *Planning and Decision-making*, the stem, “My partner and I making decisions together rather than separately is an effective strategy” is used. The items for each of the three subscales were the same as the items used for the *Preferences for Sexual Health Outcomes Scale*. The *Couple Efficacy to Reduce HIV Threat Scale* defines couple efficacy as a couple’s confidence that together they can engage in communal coping efforts. The study also assesses the occurrence of violence within the relationship using the Conflict Tactics Scale Revised [64] to assess both perpetration and experience of IPV.

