## Results

Stronger Together was launched in August 2014. To date, 160 couples (97% of the target enrollment) have been enrolled and randomized. The average retention rate across the surveys is 95%: current retention at 24 months is >90% across sites. Relationship dissolution has been relatively low, with only 13 couples breaking up during the RCT (13/160, 8%). Of the 13 couples who have broken up, 10 of the 13 (77%) HIV-positive partners have been retained in the cohort; none of these HIV-positive partners have enrolled new partners in the RCT.

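### The safety comparison is set at the level of the individual man, with tests that assume independence, although couples are randomised and partners share or jointly report the outcomes

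*Protocol article*

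**What the plan says.** All references are to the protocol article.

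- *Randomization*: the unit allocated is the couple: "couples are randomized to either the control arm (Individual Counseling) or the intervention arm (Couples Counseling").
- Safety paragraph (at the end of *Incidence of Aggregate Sex at Risk Within Partnerships*): "The safety of the intervention at the individual level will be assessed by examining reported IPV within the relationship and relationship dissolution". Each adverse outcome, and a composite of any of them, is tabulated as a prevalence, and "prevalence of outcomes will be compared in the control and intervention groups using Chi-square tests or Fischer’s exact tests, as appropriate". No denominator is given and no couple adjustment is named.
- *Process and Use of Communal Coping*: the violence scale is used "to assess both perpetration and experience of IPV", so each man reports on what he did and what was done to him in the same relationship.
- *Results*: dissolution is reported per couple, 13 of 160 (8%).
- Elsewhere the couple is taken into account. For the dyadic scales, "These analyses will include participant-level characteristics and couple-level variation or clustering". For at-risk sex, a GEE model treats the couple as the repeated unit.

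**The concern.** Chi-square and Fisher's exact tests require independent observations. Two men in one couple are allocated together and are not independent on these outcomes. A break-up is a single event that belongs to both. Violence is reported by both about one relationship, so their answers are probably related, though they need not agree.

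If each man is a row, the table appears to hold twice as many independent units as were randomised, and the test rejects too often under the null. IPV and dissolution are the trial's named safety measures, so a couples intervention could appear to differ from control, in either direction, on evidence weaker than the p-value suggests.

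This is more than a detail left to an unseen analysis plan. The article itself states the level, the outcomes and the tests, and that combination is what fails.

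**Working it through.** **Inputs from the article.** Couples are randomised. An odd or even random number decides the arm, so allocation is nominally about 1:1. There are 13 break-ups among 160 couples, arms pooled.

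**Assumptions.** Two-sided alpha of 0.05 for safety (the article gives 95% confidence for sample size and two-sided tests for the scales, but nothing for safety); 80 v 80 couples; within-couple correlation (ICC) for IPV between 0 and 1; both partners contribute a row.

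**Step 1: the article's own figure.** 13/160 = 8.1%, which agrees with the stated 8%. The denominator is couples. No power or error rate is stated for safety, so nothing else can be reproduced.

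**Step 2: true level if men are the rows.** For clusters of two, design effect = 1 + (2 − 1) × ICC = 1 + ICC. The true level of an unadjusted nominal 5% test is 2 × [1 − Φ(1.96/√(1 + ICC))].

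| ICC | Design effect | 1.96/√(design effect) | True level |
|---|---|---|---|
| 0 | 1.00 | 1.960 | 5.0% |
| 0.25 | 1.25 | 1.753 | 8.0% |
| 0.5 | 1.50 | 1.600 | 11.0% |
| 0.75 | 1.75 | 1.482 | 13.8% |
| 1 (dissolution) | 2.00 | 1.386 | 16.6% |

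**Step 3: check by simulation for dissolution.** 100,000 replicates, 80 couples per arm, the same 8.125% risk in both arms:

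| Rows | Chi-square | Fisher's exact |
|---|---|---|
| Couples (each break-up once) | 4.6% | 2.6% |
| Men (each break-up twice) | 16.8% | 13.2% |

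The Chi-square result by men agrees with the 16.6% from Step 2. Fisher's test does not cure the problem. With couples as rows, both tests keep their level.

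**Step 4: illustration.** The split by arm is not reported, so these splits of the 13 break-ups are hypothetical. For 9 v 4 of 80 couples, Chi-square = 160 × (9 × 76 − 71 × 4)² / (80 × 80 × 13 × 147) = 2.09. Doubling every cell doubles the statistic to 4.19.

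| Split (couples) | Test | p by couple | p by man |
|---|---|---|---|
| 9 v 4 | Chi-square | 0.148 | 0.041 |
| 9 v 4 | Fisher | 0.247 | 0.064 |
| 10 v 3 | Chi-square | 0.043 | 0.004 |
| 10 v 3 | Fisher | 0.079 | 0.007 |

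At 9 v 4 only the Chi-square test crosses 0.05 when the unit changes; at 10 v 3 only Fisher's test does. The data are the same in each row; only the unit differs.

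**The case against.** The best defence is that the phrase about the individual level need not define the rows of a table. In the next sentence, the word individual applied to an adverse outcome most naturally means separate. The only dissolution figure in the article is per couple. The preceding paragraph uses almost the same Chi-square/Fisher sentence directly after percentages of couples. With couples as rows, the named tests are valid for dissolution.

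Part of this stands. A reader might infer that the plan does count each break-up twice. The article does not say so, and the double count is conditional on a literal reading. But the same comparison cuts the other way: the article writes couples in the preceding paragraph and individual level here. The safety text and the Results section therefore point to different units. For IPV, which each man reports for himself, nothing in the article points to a couple-level count.

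Three further inferences are not supported:

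- **That the dyadic-scale analysis has the same fault.** It says "Participants will be nested within couples with the participant as the experimental unit", which is loose wording in a couple-randomised trial. But the same sentence nests men within couples, and the one before it includes couple-level clustering. No standard error is shown to be wrong there.
- **That safety confidence intervals will be too narrow.** None are planned; only prevalences and tests are.
- **That harm could be hidden.** The error makes differences look more certain. Nor does any decision rule in the article depend on a safety p-value.

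**Conclusion.** The point holds in conditional form. The article fixes an individual level and independence-based tests for outcomes that are shared or jointly reported within the randomised unit, and it makes no allowance for the couple. Followed literally, a nominal 5% Chi-square test has a true level of 16.6% for dissolution. For IPV it lies between 5.0% and 16.6%, depending on a correlation that the article does not give; 11.0% corresponds to an assumed 0.5. If dissolution is analysed per couple, as the Results section reports it, there is no error for that outcome, and the problem is confined to IPV and the composite.

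The levels rest on alpha 0.05, a non-negative within-couple correlation and both partners contributing rows. The simulation and the illustrative p-values also assume 80 v 80 couples, and the splits are invented. The consequence is overstated evidence of a safety difference, in either direction. It should be corrected before analysis, because these are the trial's only named safety outcomes and the remedy is simple.

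**What to change.** Amend the safety paragraph only, by stating the unit for each outcome:

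- **Dissolution:** one record per randomised couple, compared by Chi-square or Fisher's exact test on couples. This also brings the paragraph into line with the Results section.
- **IPV and any adverse outcome:** either a couple-level indicator (reported by either partner), compared by the same tests, or an analysis by man using GEE or robust standard errors clustered on the randomised couple. Choose one as the main analysis. GEE is already planned for other outcomes in the article.

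The dyadic-scale section needs no change. The cost is a few words of analysis text and less extreme p-values. No new data, visits or participants are needed.
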